## Abstract

**Background:**

The 2019 Canada’s Food Guide provides universal recommendations to individuals aged ≥2 years. However, the extent to which these recommendations are appropriate for older adults is unknown. Although ideal, conducting a large randomized controlled trial is unrealistic in the short term. An alternative is the target trial emulation framework for causal inference, a novel approach to improve the analysis of observational data.

**Objective:**

This study aims to describe the protocol for a target trial emulation in older adults, with an emphasis on key aspects of a hypothetical sustained diet and physical activity intervention.

**Methods:**

To emulate the target trial, nonexperimental data from the Quebec Longitudinal Study on Nutrition and Successful Aging (NuAge; N=1753 adults aged ≥67 years) will be used. NuAge includes 4 yearly measurements of dietary intakes, covariates, and outcomes. The per-protocol causal contrast will be the primary causal contrast of interest to account for nonadherence. The sustained intervention strategy will be modeled using the parametric g-formula. In the hypothetical trial, participants will be instructed to meet sex-specific minimal intakes for vegetables and fruits, whole grains, animal- and plant-based protein foods, milk and plant-based beverages, and unsaturated fats. The eligibility criteria, follow-up, intervention, outcomes, and causal contrast in the emulation will closely align with those of the target trial, with only minor modifications. We will attempt to emulate the randomization of treatment by adjusting for baseline covariates and prebaseline dietary habits.

**Results:**

Data collection for NuAge was completed in June 2008. For this study, the main analysis was started in May 2024. Submission of the manuscript is expected by February 2025.

**Conclusions:**

Emulating a target trial will provide the first evidence of the adequacy of the 2019 Canada’s Food Guide recommendations for older adults in relation to health outcomes.

**International Registered Report Identifier (IRRID):**

DERR1-10.2196/65182

## Introduction

### Background

The latest edition of Canada’s Food Guide (CFG) was published in 2019 [1]. Compared with the previous edition, key changes include the removal of the prespecified number of servings to consume each day, a shift toward qualitative (eg, “eat plenty of...”) instead of quantitative recommendations, and the provision of universal recommendations instead of age- and sex-specific recommendations. In addition, CFG recommendations primarily aim to reduce chronic disease risk. The evidence supporting CFG recommendations focuses on reducing the risk of cardiovascular disease, cancer, and type 2 diabetes risk [2]. However, evidence from a nationally representative survey of adults aged ≥65 years from Canada suggested that greater adherence to recommendations was insufficient to meet calcium, vitamin D, and folate requirements [3]. In Canada, one-third of community-dwelling older adults are at high nutrition risk [4,5], highlighting the importance of maintaining adequate nutritional status in this stratum of the population. Similarly, in the absence of specific recommendations on the amount of protein foods to eat, older adults may be eating less protein than required to maintain muscle mass [6-8]. CFG also provides brief physical activity recommendations but without explicit acknowledgment of the importance of these recommendations for older adults [1]. Indeed, performing a minimal amount of physical activity is paramount to maintaining muscle mass [6,7]. Thus, the universal recommendations in CFG may not be appropriate for older adults because they face unique challenges in consuming a healthy diet [9] and may require specific nutritional strategies [10].

Ideally, a randomized controlled trial (RCT) should be conducted to investigate the adequacy of CFG recommendations in older adults. However, such an RCT is unlikely to be conducted in the short term. An alternative is the target trial emulation framework for causal effect estimation using observational data [11-14]. Informally, the target trial emulation framework aims to emphasize and resolve design challenges in observational data analysis by explicitly emulating a hypothetical trial to estimate a causal effect [11]. In nutritional epidemiology, common issues with design and analyses can yield results that are largely inconsistent with those of randomized trials [15]. For example, the lack of consideration of the compositional nature of diet can dramatically influence effect estimates, that is, increasing the intake of one food must be compensated by decreasing the intake of another food in substitution modeling [15-17]. Furthermore, diet is a lifelong sustained exposure. In an observational study, the effect of diet assessed at a given time may actually reflect the cumulative exposure to previous dietary habits. In turn, ignoring previous dietary habits may result in a misalignment of “time zero” [18], as dietary habits are not randomly assigned at the beginning of the observational study. In other words, ignoring previous dietary habits makes it impossible to distinguish the effect of prospective or hypothetical dietary modification from the effect of retrospective dietary habits. The target trial framework is a helpful tool to highlight and address common issues in nutritional epidemiology. Ultimately, a successful emulation of the target trial based on observational data could yield effect estimates that more closely align with those of a hypothetical future RCT. Example applications of the target trial framework include the emulation of interventions on diet [19-22], physical activity [23], or both [24].

### Objectives

To the best of our knowledge, a target trial framework has not been used to assess the effect of adhering to CFG recommendations. Accordingly, this study aims, first, to describe the protocol for the emulation of a target trial using observational data from the Quebec Longitudinal Study on Nutrition and Successful Aging (NuAge [25]), which includes a cohort of 1753 adults aged 67 to 84 years at baseline, and, second, to address key aspects of the target trial emulation in the context of a sustained lifestyle intervention strategy involving diet and physical activity. Key aspects are the description of the sustained lifestyle intervention strategy, the attempt to emulate randomization, as well as assumptions and limitations specific to diet intervention. Notably, more general introductory texts to the target trial framework are available elsewhere [11,12,14].

## Methods

### Research Question and Hypothesis

Explicitly acknowledging the causal nature of a research question is a prerequisite to causal effect estimation using observational data [26-28]. This study aims to examine the adequacy of the universal dietary recommendations provided by CFG for older adults. Expressed as a counterfactual statement, we aim to answer the following question: What would be the difference in a given health outcome at the end of the follow-up if all eligible participants had increased their adherence to CFG recommendations on healthy food choices, compared to if they had maintained their habitual diet?

Specifically, among adults aged 67 to 84 years followed for 3 years, and compared with maintenance of habits, we aim to (1) estimate the causal effect of adhering to CFG dietary recommendations on markers of muscle health (eg, physical function and muscle strength), general health (eg, waist circumference, blood pressure, and glucose), and cognitive health (ie, Modified Mini-Mental State Examination) and (2) estimate the causal effect of adhering to a *reformulation* of CFG dietary recommendations, including more protein foods and a minimal physical activity recommendation, to amplify the positive health effects.

Accordingly, we hypothesize the following:

*Hypothesis 1: adhering to recommendations positively influences general and cognitive health but does not influence muscle health.*

*Hypothesis 2: increasing the consumption of protein-rich foods positively influences muscle health, and meeting minimal physical activity recommendations (≥30 min per day) further amplifies positive health effects.*

### Study Design and Sample

Data from the NuAge prospective cohort will be used to emulate the target trial [25]. The NuAge cohort comprised 1753 generally healthy community-dwelling adults aged 67 to 84 years at baseline and followed for 3 years. The baseline and each annual follow-up evaluation included a comprehensive assessment of sociodemographic data, diet, physical activity, functional status, as well as physical and mental health status [25].

The NuAge sample is relevant to our research question. The target population of CFG recommendations comprises all individuals aged ≥2 years, which is compatible with the NuAge target sample of generally healthy older adults from the greater Montreal, Sherbrooke, and Laval areas of the province of Quebec, Canada.

### Target Trial

The target trial framework has been suggested as a potential solution to improve the analysis of nutritional epidemiology studies aiming at causal inference [13]. Informally, the target trial framework helps to align the observational data analysis with that of a hypothetical trial. This framework is appropriate for the research question in this study, as we aim to estimate the effect of adhering to a hypothetical diet and physical activity intervention using observational data. The first step of a target trial emulation is the description of the target trial, that is, the protocol for the hypothetical RCT we wish to conduct [11,14]. The second step is the emulation, that is, describing how the target trial is emulated and conducting the study described in this protocol.

Table 1 presents the target trial and its emulation using observational data from NuAge. Key differences between the target trial and its emulation are that participants will be required to provide complete dietary assessment and covariate data at baseline (ie, eligibility component) and that we will attempt to emulate the randomized assignment by adjusting for dietary intakes before baseline as well as baseline covariates (ie, assignment component). Each part of the target trial and its emulation are described in the subsequent sections.

**Table 1 table1:** Emulation of a dietary intervention target trial using observational data from the Quebec Longitudinal Study on Nutrition and Successful Aging (NuAge [25]).

Trial component	Target trial specification	Target trial emulation
Eligibility criteria	NuAge inclusion criteria: individuals aged 67-84 years; living in Montreal, Laval, or Sherbrooke; not cognitively impaired; and free of disabilities in activities of daily living Exclusion criteria: class II heart failure, chronic obstructive pulmonary disease requiring home oxygen therapy or oral steroids, inflammatory digestive diseases, and cancer treatment in the past 5 years	The inclusion and exclusion criteria are the same as those specified in the target trial. Furthermore, participants will be required to have complete baseline dietary assessment (at least one 24-hour recall with ≥500 kcal and FFQ^a^) and provide baseline covariate data.
Interventions^b^	Each individual would be assigned to 1 of the 4 following strategies: Control group (habitual diet, ie, typical North American diet) Adherence to Canada’s Food Guide recommendations on healthy food choices Adherence to Canada’s Food Guide recommendations on healthy food choices and including a high-protein reformulation Adherence to Canada’s Food Guide recommendations on healthy food choices, including a high-protein reformulation and a minimal physical activity component Each strategy is followed until the end of follow-up. Participants assigned to a lifestyle strategy are expected to maintain their dietary intake or amount of physical activity at or above the prespecified threshold by the corresponding intervention strategy.	The intervention component will be the same as that specified in the target trial. Furthermore, we will assume that each dietary assessment period (ie, within 2 months beginning at each time point) accurately reflects the average diet in the interval between follow-ups.
Assignment	Participants are randomly assigned to a dietary strategy but are not blinded to their assignment.	We will attempt to emulate randomized assignment by adjusting for dietary intakes before baseline and baseline covariates.
Outcomes	The outcomes are physical function and muscle strength, general health indicators, and cognitive health.	The outcomes will be physical function and muscle strength, general health indicators, and cognitive health.
Time zero and follow-up	The study starts at baseline and ends at incomplete follow-up or 3 years after baseline, whichever occurs first.	The study will start at baseline and end at incomplete follow-up or 3 years after baseline, whichever occurs first. An incomplete follow-up is defined as missing data for questionnaires (nonresponse or loss to follow-up) or missing outcome data at the end of follow-up.
Causal contrast^c^	Intention-to-treat effect Per-protocol effect	Observational analog of both contrasts: Secondary: intention-to-treat effect Primary: per-protocol effect
Statistical analysis	Intention-to-treat analysis: apply inverse probability weighting with adjustment for prebaseline and baseline factors associated with incomplete follow-up to account for study dropouts Per-protocol analysis: apply the parametric g-formula algorithm to compare postintervention outcomes between groups receiving each treatment strategy, adjusting for pre- and postbaseline factors associated with adherence to intervention strategies and incomplete follow-up.	Analysis will be the same as that specified in the target trial for both contrasts. However, the observational analog will require additional adjustments for confounding at baseline and before baseline due to previous dietary pattern.

^a^FFQ: food-frequency questionnaire.

^b^Refer to the *Hypothetical Interventions* section for detailed intervention.

^c^The observational analog of the intention-to-treat contrast corresponds to the baseline values of the intervention, which are assigned and initiated at the same time.

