### Assignment

We will attempt to emulate random allocation or randomization by adjusting for dietary intakes in the year before the intervention, as well as adjusting for covariates at the start of the study. Covariates were identified using the causal diagrams depicted in Figure 1, based on background knowledge of the relationship between the hypothetical lifestyle intervention and outcomes.

Dietary components that are the foundation for healthy eating in CFG include intakes of vegetables and fruits, whole grains, protein foods (plant- and animal-based protein foods, milk, and plant-based beverages with protein), and unsaturated oils and fats [1].

Covariates, including age at baseline, biological sex, region, education, living alone, smoking and drinking (alcohol) habits, major chronic diseases (ie, hypertension, diabetes, cancer, and heart disease), the number of medications, supplement use (eg, vitamins and minerals), and height and weight, are as follows:

*Z*, baseline covariates: age, sex, region, education, history of smoking, height, and former cancer history*P*, previous exposure (ie, exposure of time-varying intervention before baseline): dietary habits before baseline*L*, (time-varying) covariates: weight, number of medications, supplement use, living alone, major chronic diseases (eg, hypertension, diabetes, cancer, and heart disease), and smoking and alcohol habits*X*, (time-varying) treatment: diet and physical activity habits*Y*, end of follow-up outcome: muscle health, general health, and cognitive health

Contrary to dietary habits, data on physical activity habits before baseline were not collected in NuAge. In this case, the potential effect of previous physical activity habits will not be accounted for in the models that aim to emulate the sustained physical activity intervention strategy. For the models emulating the sustained diet intervention strategy only, physical activity habits during the study will be used as a covariate, hence mitigating the confounding of previous physical activity, at least to some extent.

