### Time Zero and Follow-Up

In the target trial of a sustained lifestyle intervention, participants would be met at baseline and then regularly to ensure that diet and physical activity habits are consistent with the intervention assigned by the random allocation. The hypothetical diet and physical activity intervention would be assigned and initiated at baseline. In the emulation, annual follow-ups with comprehensive diet, physical activity, and covariate data collection are available to emulate the hypothetical intervention. Hence, participants would be followed from the study baseline (time point 0; ie, the time at which the intervention strategy would also be assigned and would begin), at each year (ie, time points 1 and 2), and until the end of the study (time point 3). We also assume that the diet and physical activity habits measured at each follow-up time adequately reflect the habits during the entire year.

The end of follow-up outcome measurements will be used to estimate the effect of the sustained lifestyle intervention strategy. Measures of dietary intake and physical activity throughout the study (ie, time point 0 to time point 3) will be used to emulate the sustained lifestyle intervention. Dietary intakes in the year preceding the intervention will be estimated using the frequency questionnaire completed at baseline (ie, time point 0). Missing covariate data at a given follow-up will be carried forward once, after which participants will be considered as having incomplete follow-up.

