#### Dietary Assessment

In NuAge, diet during the year before baseline was assessed using 1 semiquantitative food-frequency questionnaire [47]. Dietary intakes at baseline (ie, time point 0) and each annual follow-up (ie, time points 1, 2, and 3) were assessed using 3 repeated face-to-face interviewer-administered 24-hour dietary recalls.

Dietary intakes measured using 24-hour dietary recall are more accurate (ie, have less systematic error or bias) than food-frequency questionnaire [48-50] but are particularly affected by random measurement error (ie, within-individual random error) [50]. When several variables measured with errors are considered simultaneously in a regression model, the regression coefficients may be biased in any direction [51]. To account for random measurement error, the National Cancer Institute Markov Chain Monte Carlo (NCI MCMC) multivariate method could be applied [52]. However, the combination of the parametric g-formula and multivariate measurement error correction using the NCI MCMC method is not feasible. The NCI MCMC method estimates time-invariant measurement error–corrected intakes, while the g-formula algorithm is designed for time-varying exposures.

Recognizing the importance of accounting for measurement error, the correction for measurement error will be reserved for the secondary intention-to-treat analysis. For the intention-to-treat contrast, the time-varying values of exposure and the time-varying values of confounding are not considered. Thus, the NCI MCMC method will be used to obtain measurement error–corrected estimates of the relationship between dietary intakes measured at baseline and outcome at the end of follow-up. Notably, the three 24-hour dietary recalls collected at each time point contribute to reducing random errors, at least to some extent, even in the absence of measurement error correction.

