#### Physical Activity Assessment

Physical activity throughout the study will be assessed using the Physical Activity Scale for the Elderly questionnaire [53,54]. Rather than the total Physical Activity Scale for the Elderly score, specific questions estimating the total time of physical activities will be used to be consistent with the intervention strategy.

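### Diet is sampled in a short window at annual visits and season is in no adjustment set, so season of assessment can confound both contrasts if it affects both measured exposure and outcome

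*Protocol article*

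**What the plan says.** **Diet.** Under Dietary Assessment, intakes at time points 0 to 3 "were assessed using 3 repeated face-to-face interviewer-administered 24-hour dietary recalls". The emulation column of Table 1 (Interventions row) assumes that "each dietary assessment period (ie, within 2 months beginning at each time point) accurately reflects the average diet in the interval between follow-ups".

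**Activity.** "Physical activity throughout the study will be assessed using the Physical Activity Scale for the Elderly questionnaire", using the items on time spent active. No sampling window or recall period is stated.

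**Timing.** Time Zero and Follow-Up says that "annual follow-ups with comprehensive diet, physical activity, and covariate data collection are available to emulate the hypothetical intervention", and assumes that "diet and physical activity habits measured at each follow-up time adequately reflect the habits during the entire year". The outcome is the value at time point 3. No calendar months or visit tolerances are given.

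**Adjustment.** The Assignment section itemises the sets. Z is "baseline covariates: age, sex, region, education, history of smoking, height, and former cancer history". L is "time-varying) covariates: weight, number of medications, supplement use, living alone, major chronic diseases (eg, hypertension, diabetes, cancer, and heart disease), and smoking and alcohol habits". P is diet before baseline, taken from one food-frequency questionnaire covering the previous year. The section then assumes that these covariates suffice to deal with confounding. Season and date of assessment appear in none of the sets, nor anywhere else in the article.

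**The concern.** A window of at most 2 months, repeated at 12-month spacing, tends to catch each person at a similar point of the year. If measured intake or activity varies with season, that deviation does not average out over four waves. It repeats, and in the data it resembles a sustained difference in adherence, which is the exposure in the primary per-protocol contrast. The outcome visit is the last of these annual visits and may carry the same season. If the outcome also varies with season, season is a common cause of exposure and outcome that the adjustment set omits. The intention-to-treat analog is exposed in the same way when the baseline and final visits fall in the same season.

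**Working it through.** The plan gives no figure to reproduce here. The check has two parts: whether any planned step would deal with season, and what size of bias is conceivable.

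**1. Planned safeguards**

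- *Three recalls per wave* reduce day-to-day random error. A deviation shared by all recalls in one window stays.
- *The NCI MCMC correction* targets within-person random error and is reserved for the secondary intention-to-treat analog.
- *The prior-year questionnaire (P)* captures stable habit, not the season of the later recalls. It covers diet only; the Assignment section says that earlier activity was not collected.
- *The comparison of observed with predicted covariates*, described in the Discussion, tests model fit, not an omitted common cause.

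None of these would detect or remove a seasonal deviation.

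**2. Illustration on a blood pressure scale (all inputs assumed, true effect zero)**

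Usual intake U has SD 1.5 RA/d, recall error per wave has SD 1.5 and questionnaire error has SD 1.5. Measured diet is X_k = U + A·cos(month) + error, and the outcome is Y = B·cos(month) + noise. Y is regressed on P and X_0 to X_3, and the sum of the four X coefficients is multiplied by a 2 RA/d increase.

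Same month at every visit:

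- Var(U given P) = 2.25 − 2.25²/4.5 = 1.125.
- Error variance of the four-wave mean = 2.25/4 = 0.5625.
- Spurious effect = 2 × (AB/2) / (1.125 + 0.5625 + A²/2) = AB / (1.6875 + A²/2).

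Month independent at each visit, so that only X_3 shares a season with Y:

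- Spurious effect = 2 × (AB/2) / (2.25 + A²/2 + 4 × 1.125) = AB / (6.75 + A²/2).

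| A (RA/d) | B (mm Hg) | Same month | Independent months |
|---|---|---|---|
| 0.25 | −1 | −0.25/1.719 = −0.15 | −0.25/6.781 = −0.04 |
| 0.5 | −2.5 | −1.25/1.8125 = −0.69 | −1.25/6.875 = −0.18 |
| 0.75 | −4 | −3/1.969 = −1.52 | −3/7.031 = −0.43 |

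Simulations with n = 400,000 agree: −0.14 to −0.15, −0.69 and −1.51 to −1.54 for the same month; −0.04, −0.18 and −0.42 for independent months. With sine and cosine of month in the model, the effect is about 0.

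These results depend strongly on the assumptions:

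- *Phase.* If the two cycles are offset by an angle φ from exact opposition, the result is multiplied by cos φ. A 2-month offset (60°) halves it (−0.07, −0.34, −0.76). A 3-month offset (90°) gives about 0.
- *Visit timing.* If follow-up visits vary with SD 2 months, simulation gives −0.09, −0.40 and −0.92.
- *Amplitude.* If A = 0 or B = 0, AB = 0 and there is no bias.

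**3. Illustration with a threshold intervention**

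This follows the plan's type of strategy more closely: every wave is raised to the 90th percentile of measured intake. Usual intake has SD 1, questionnaire error SD 0.7 and recall error SD 0.8, with n = 400,000 and a true effect of zero. Diet amplitude is in usual-intake SD; outcome amplitude and results are in outcome SD.

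| Diet amplitude | Outcome amplitude | Season fixed, unadjusted | Season terms added | Season random by wave, unadjusted |
|---|---|---|---|---|
| 0 | 0.2 | −0.005 | −0.005 | −0.002 |
| 0.2 | 0 | −0.002 | −0.002 | −0.003 |
| 0.2 | 0.1 | 0.035 | 0.000 | 0.013 |
| 0.3 | 0.2 | 0.094 | −0.004 | 0.025 |
| 0.5 | 0.2 | 0.153 | 0.009 | 0.046 |

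Simulation noise is about ±0.01. Conditioning on the prior-year questionnaire did not remove the bias.

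**The case against.** The whole-year assumption is declared, not hidden. The article also says that absence of unmeasured confounding cannot be guaranteed, and concedes that the assumption of no measurement error will not be met. There is no contradiction and no wrong figure. On this view the point is only a request for one more covariate in a condensed article whose full analysis plan is not shown.

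Part of this stands: the article is candid about its assumptions. But it does not leave the adjustment set open. It lists the set item by item and assumes that it is sufficient, and its limitations discuss random recall error without raising season.

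The objection to the numbers is stronger. Every amplitude is assumed. The blood pressure illustration sets the two cycles exactly opposite, uses a secondary outcome, and omits the total food and total beverage terms that the plan puts in all models. The near-zero result after adjustment is built in, because season is the only source of bias simulated. All of this stands, so the figures show a mechanism and do not estimate its size in NuAge.

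A reader might also infer that every visit falls on the same calendar date, or that activity is sampled in the same 2-month window as diet. The documents support neither. Similar timing is inferred from annual spacing, and the window is stated for dietary assessment only; for activity there is only the whole-year assumption. Even so, with months independent at each wave the per-protocol bias shrinks without vanishing, because diet at time point 3 still shares a season with the outcome.

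**Conclusion.** The point holds as a conditional one. The whole-year assumption is untested, season of assessment is a possible common cause left out of a fixed adjustment set, and no planned analysis would reveal it. It can bias the per-protocol and intention-to-treat contrasts if season affects both the measured exposure and the outcome. The size cannot be derived from the documents. In the threshold illustration it ran from about 0 to about 0.15 outcome SD with season fixed per person, and up to about 0.05 SD with season random by wave.

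It would be tempting to conclude that season does confound the primary contrast. The documents do not support that. They give no seasonal amplitude for intake, activity or any outcome, and no bias has been shown for the primary outcomes of muscle strength and physical function. The change is nevertheless worth making, because it is specific and cheap.

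**What to change.** First establish whether assessment dates or months are in the analysis dataset; the article does not say. Where they are, add calendar time of assessment (sine and cosine of date, or season) to the covariate, outcome and dropout models of both the per-protocol and intention-to-treat analyses. Enter it per time point if a participant's visits shift through the year. At minimum, run a season-adjusted sensitivity analysis of both contrasts.

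Qualify the assumption in Table 1 and in Time Zero and Follow-Up: measured diet and activity are taken to represent the year after adjustment for season of assessment. If neither dates nor months are available, list unadjusted season among the limitations.

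The cost is one entry in the covariate list and about two degrees of freedom per model, which is modest even in a cohort of 1753 that the article itself calls relatively limited.
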